### Outcomes

The primary outcome measure is recurrence needing revision surgery within 12 months postoperatively. Secondary outcome measures include: (1) complication (morbidity) within 12 months postoperatively; (2) mortality within 12 months postoperatively; (3) Markwalder Scale, mRS, and Glasgow Outcome Score; and (4) radiological characteristics of postoperative CT images at 24 hours and 6 weeks. On axial CT scans, the midline shift is measured in millimeters at the level of the foramina of Monro and the thickness of the hematoma at the thickest area.

### Sample Size

Initially the study was planned as a superiority study to show a significant difference in the recurrence rate of cSDH between insertion of an SPD and an SDD. When estimating the sample size, a difference in the recurrence rate of 10% in the SDD group versus 20% in the SDP group was assumed (based on Bellut et al and Santarius et al [2,5]), leading to the estimate of 150 patients in each group. New studies [12] and the blind data review of the first 56 patients (both groups pooled) suggested a lower recurrence rate of 7%. Therefore the sample size was reviewed. At the same time, the study design was changed from a superiority to a noninferiority design, and a noninferiority margin of 3.5% was defined.

We reestimated the recurrence rates in a blinded manner based on the overall recurrence rate. Since no hypothesis test was performed, no *P* value adjustment to control type I error was needed. Data from all patients who had a follow-up visit could be used for the sample size review. When reestimating the recurrence rates, it was assumed that the probability of being in one group or the other (SDD vs SPD) for patients who had a follow-up visit would be equal. As stated the reestimated recurrence rate was 7%, which was the expected difference between the SDD group and SPD group (3.5%−10.5%=7%). Using the reestimated recurrence rates, the sample size N was reestimated using a resampling procedure. Each sample size, N_i=1;...;101_=50;...;150, was evaluated by sampling 9999 times N_i_ individual samples based on the assumptions described above. Confidence intervals (CIs) for the difference between proportions were calculated using a continuity-corrected modification of the Wilson score method. Sample size was set to ensure with 80% power (1–β=0.8) (ie, in 80 of 100 hypothetical repetitions of the study) the estimation of a 95% CI, which is entirely below the predefined noninferiority margin of 3.5%.

For this study, a total of 220 patients should be randomized to ensure 208 evaluable patients (110 patients randomized per study arm) (Figure 2) considering an overall drop-out rate of 5% after randomization (eg, death, lost to follow-up).

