### Participant Timeline

Patient admission.Clinical evaluation and cranial CT (if none exists).Obtain informed consent.If the patient is treated with vitamin K antagonist, preoperative reversal using Beriplex and Konakion is done aiming for a preoperative international normalized ratio of 1.3. In patients treated with Aspirin Cardio or Plavix, the medications should be discontinued and surgery postponed for 5 to 7 days if possible. If emergency surgery is indicated, the Aspirin Cardio or Plavix should be discontinued preoperatively and for 2 to 6 weeks postoperatively depending on the indication for treatment (see step 12).Surgical evacuation of the cSDH with burr-hole trepanation.Randomization: SDD group versus SPD group.Monitoring in the intermediate or intensive care unit.Cranial CT and clinical evaluation 24 hours postoperative.Low-weight molecular heparin in prophylactic dosage is given postoperatively with mobilization of the patient (with the drainage pinched off) after 24 to 48 hours.Drain removal after 36 to 48 hours.Patient discharge after clinical evaluation on postoperative day 5 or later.Resumption of Aspirin Cardio or Plavix no earlier than 2 weeks postoperatively for patients with secondary prophylaxis and 6 weeks postoperatively for patients with primary prophylaxis. Resumption of Marcoumar should be no earlier than 6 weeks postoperatively.Clinical evaluation and cranial CT at the outpatient clinic 6 weeks postoperatively (±2 weeks).Clinical evaluation at the outpatient clinic 12 months postoperatively (±4 weeks).

See Multimedia Appendix 1 for a time schedule of enrollment, interventions, assessments, and visits for participants. The flow diagram (Figure 1) illustrates the key steps of the trial.

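### The 7% recurrence rate behind the redesign may understate the 12-month endpoint rate, because the blinded review admitted any patient with a follow-up visit

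*Protocol article*

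**What the plan says.** The Outcomes section fixes the endpoint: "The primary outcome measure is recurrence needing revision surgery within 12 months postoperatively". The Participant Timeline has two outpatient visits: "Clinical evaluation and cranial CT at the outpatient clinic 6 weeks postoperatively (±2 weeks") and "Clinical evaluation at the outpatient clinic 12 months postoperatively (±4 weeks").

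The Sample Size section explains why the first assumption, 10% against 20%, was dropped. It cites newer studies (reference 12) and adds that "the blind data review of the first 56 patients (both groups pooled) suggested a lower recurrence rate of 7" per cent. On eligibility for that review it says: "Data from all patients who had a follow-up visit could be used for the sample size review". The re-estimated rate is then turned into arm rates, the 7 points being the figure "which was the expected difference between the SDD group and SPD group (3.5%−10.5%=7" per cent). In the same step "a noninferiority margin of 3.5% was defined". The resulting size is 220 randomized and 208 evaluable patients: "Sample size was set to ensure with 80% power".

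The article does not give the date of the review or the follow-up reached by the 56 patients.

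**The concern.** The stated rule admits a patient whose only outpatient visit was at 4 to 8 weeks. If such a patient enters a crude proportion as recurrence-free, any reoperation between the data cut and month 12 is not counted. Incomplete follow-up can hide later events but cannot add any, so bias from this source can only be downward.

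The resulting proportion is then used as the rate of a 12-month endpoint, and the stated sample size and power are calculated from it. At stake is whether those figures describe the trial that will be analysed. The same issue arises in the Monitoring section, which plans yearly interim analyses of the recurrence rate. At a look taken during or soon after enrolment, some patients will again lack 12 months of follow-up.

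**Working it through.** **Inputs from the article.** Endpoint window 12 months. Outpatient visits at 6 ± 2 weeks and 12 months ± 4 weeks. Pooled rate 7% with 56 patients reviewed. Arm rates 3.5% and 10.5%. Margin 3.5 points. 95% CI, taken as two-sided, by a continuity-corrected Wilson score method. 208 evaluable patients, so 208/2 = 104 per arm.

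**Assumptions.** A follow-up visit means an outpatient visit. The lower rate belongs to the SPD arm: the article prints the arms in the other order, but the stated size reproduces only this way round.

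**Step 1: reproduce the plan's figure.** Noninferiority is shown when the upper limit U for SPD minus SDD is below 0.035, where

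U = (p1 − p2) + √[(u1 − p1)² + (p2 − l2)²],

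with u1 and l2 the continuity-corrected Wilson limits of the SPD and SDD rates. Power is the sum of the binomial probabilities of all outcomes with U < 0.035, enumerated exactly instead of resampled. With 3.5% and 10.5%:

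- 104 per arm: 78.5%
- 110 per arm: 82.6%
- smallest size holding 80%: 109 per arm

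This is within 2 points of the stated 80%, so the plan's calculation is reproduced.

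**Step 2: precision of the 7%.** The nearest count is 4, since 4/56 = 7.1%; it is inferred, not stated. The exact (Clopper-Pearson) 95% CI is 2.0% to 17.3%.

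**Step 3: how far 7% could lie below the 12-month rate.** Let f be the share of the 56 with a full 12 months, and g the share of 12-month recurrences already seen by the 6-week visit in the others. Then

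12-month rate = 0.07 / [f + (1 − f)g].

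Neither f nor g is in the article, so only a range can be shown:

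| f | g = 0.9 | g = 0.7 | g = 0.5 |
|---|---|---|---|
| 0 | 7.8% | 10% | 14% |
| 0.5 | 7.4% | 8.2% | 9.3% |
| 1 | 7% | 7% | 7% |

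With f = 0 and g = 0.8 the rate is 0.07/0.8 = 8.75%.

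**Step 4: power at 104 per arm if the pooled rate is higher.** The arm rates can be moved in two ways. Keeping the 7-point difference gives r − 3.5 and r + 3.5 points. Keeping the 1:3 ratio gives r/2 and 1.5r.

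| Pooled rate r | Difference kept: arms | Power | Ratio kept: arms | Power |
|---|---|---|---|---|
| 7% | 3.5% and 10.5% | 78.5% | 3.5% and 10.5% | 78.5% |
| 8.75% | 5.25% and 12.25% | 69.9% | 4.4% and 13.1% | 84.5% |
| 10% | 6.5% and 13.5% | 65.1% | 5% and 15% | 88.0% |
| 14% | 10.5% and 17.5% | 52.3% | 7% and 21% | 94.7% |

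At a pooled 10%, 80% power needs 143 per arm if the difference is kept and 87 if the ratio is kept.

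**Step 5: why the direction splits.** Compare the distance from the expected difference to the margin with its simple standard error, √[(p1q1 + p2q2)/104]:

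- Pooled 7%: distance 3.5 + 7 = 10.5 points; SE = √(0.12775/104) = 3.5 points; ratio 3.0.
- Pooled 10%, difference kept: distance 10.5; SE = √(0.17755/104) = 4.1; ratio 2.5.
- Pooled 10%, ratio kept: distance 3.5 + 10 = 13.5; SE = √(0.175/104) = 4.1; ratio 3.3.

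The variance grows almost equally in both cases, but only the second moves the expected difference further from the margin.

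**The case against.** **The follow-up may have been complete.** These were the first patients enrolled and so those followed longest. If all had reached 12 months, the bias disappears. This stands: the article shows that short follow-up was allowed, not that it occurred.

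**Events after a visit need not have been missed.** The rule says which patients contribute, not that their data stop at the visit. Under Serious Adverse Events, a recurrent event or a new hospitalization is recorded and reported within 7 days, so a reoperation between the visit and the review had another route into the data. This also stands. It confines the likely gap to follow-up time that had not yet elapsed at the review.

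**The 56 patients were not the only source.** The newer studies cited alongside them also support 7%. That is correct, although their follow-up periods cannot be seen here.

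**This is detail for the full protocol.** The length of follow-up may well be recorded there, and its absence from an article is not the criticism. The article itself states the admission rule and builds a completed design step on the result. That rule does not match the endpoint's window.

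**Two stronger readings are tempting.** A reader might infer that 7% is a floor for the true rate. An interval from 2.0% to 17.3% does not support that: the true 12-month rate could lie below 7%. A reader might also infer that the trial is underpowered. That does not follow either. The Sample Size section sets the expected difference equal to the pooled rate, with arms at half and one and a half times that rate. If that construction is carried to a higher rate, power rises.

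**Conclusion.** The point holds in a limited form. The rule for the blinded review allows follow-up much shorter than the 12 months of the endpoint, and any bias from this is downward. The 7% may therefore understate the 12-month rate, unless all 56 patients had completed 12 months.

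Its size cannot be fixed from the article. Under the assumed shares in the working, the 12-month rate lies between 7% and 14%, or between 7.4% and 9.3% if half of the patients had full follow-up. At a pooled 10%, power is about 65% or about 88%, depending on whether the difference or the ratio is kept. The supported conclusion is that the stated size and power rest on a rate not shown to be that of the endpoint. A loss of power is not established.

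**What to change.** 1. Re-derive the pooled recurrence rate, still blinded, as a 12-month Kaplan-Meier estimate from the dates of surgery, reoperation and last contact, or from patients past 12 months only. Report it with its confidence interval.
2. State in the Sample Size section how long the 56 patients had been followed. If all had reached 12 months, that sentence settles the matter for the 7%.
3. Restate the power of 220 randomized patients at that rate, under both the fixed-difference and the fixed-ratio assumption.
4. Use the same 12-month estimate for the recurrence rate at the yearly interim analyses in the Monitoring section.

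The cost is a small re-analysis of data already collected. It needs no unblinding, no extra patients and no change of endpoint. The downside is that the stated power may change.

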## Introduction

### Background

Chronic subdural hematoma (cSDH) is one of the most frequent neurosurgical conditions affecting elderly people and is associated with substantial morbidity and mortality [1-3]. Its incidence is reported to be 1.7-13.1 per 100,000 inhabitants per year, but the incidence has been steadily increasing due to prolonged life expectancy [4-6]. Surgical treatment is recommended in patients with neurological symptoms. In the only evidence-based review of the different surgical treatment modalities of cSDH, Weigel et al concluded that burr-hole craniostomy with irrigation and drainage has the best cure-to-complication ratio [7]. Recurrence is the most common complication following surgical treatment of cSDH with a rate of 0%-30% [3,4,8]. A randomized controlled study by Santarius et al showed reduced recurrence and mortality placing a subdural drain (SDD) compared to not placing a drain after burr-hole evacuation of cSDH [2]. Gazzeri et al and Zumofen et al used a closed subperiosteal drain (SPD) instead of the more commonly used SDD, and the method showed equal or superior results in outcome, complications, and postoperative symptoms compared to previous studies [9,10]. Since the SPD is not positioned in direct contact to cortical structures, bridging veins, or hematoma membranes, it is considered safer and might be favorable to an SDD. In a retrospective study, Bellut et al compared 48 patients treated with SPD to 65 patients treated with SDD and found lower mortality rates and fewer serious complications in the group treated with SPD with no difference in recurrence rate of cSDH [5]. However, none of the results showed a significant difference, and it was concluded that further randomized studies with a larger patient cohort are needed [5]. In a recently published prospective randomized study, Kaliaperumal et al concluded that the recurrence rate after placing an SPD is equal to that following placement of an SDD, with the modified Rankin scale (mRS) of the patients in the SPD group being significantly better after 6 months [11]. However, the results may have been biased since the preoperative mRS in the SPD group was inferior to those in the SDD group. In addition, the number of patients studied was small (25 per group), and the overall recurrence rate was 0%, with very low morbidity and mortality rates compared to the literature. Due to these biases the authors recommend further prospective and randomized studies with larger patient cohorts [11].

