### Aims and Objectives

The primary objective of our study is to investigate in a randomized controlled fashion whether the recurrence rate after insertion of an SPD is noninferior compared to the insertion of an SDD in patients undergoing surgical evacuation of a cSDH with burr-hole trepanation. The secondary objective of the study is to assess whether the insertion of an SPD leads to fewer operative complications, a lower mortality, and a better outcome.

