## Methods

### Trial Design

This is a prospective, multicenter, noninferiority, randomized controlled study. Eligible participants are block-randomized in a 1:1 allocation ratio to one of two arms: an intervention arm, insertion of an SPD and a control arm, insertion of an SDD.

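### The sample size section turns a pooled 7% recurrence rate into a 7-point difference between arms; the stated 80% power reproduces only if SPD is the arm with 3.5%, and at that pooled rate it is about 10% if the drains are equal

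*Protocol article*

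**What the plan says.** The primary objective (Aims and Objectives) is to establish "whether the recurrence rate after insertion of an SPD is noninferior compared to the insertion of an SDD". Allocation is 1:1 and the endpoint is reoperation for recurrence within 12 months (Trial Design; Outcomes).

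The Sample Size section gives this history:

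- The original superiority plan ran in one direction: "a difference in the recurrence rate of 10% in the SDD group versus 20% in the SDP group was assumed".
- New studies were then cited, and "the blind data review of the first 56 patients (both groups pooled) suggested a lower recurrence rate of 7" percent. The design became noninferiority with a margin of 3.5 percentage points.
- The re-estimate is described so: "As stated the reestimated recurrence rate was 7%, which was the expected difference between the SDD group and SPD group". A bracket after it sets 3.5% minus 10.5% equal to 7%. No sentence says which arm has which rate.
- On the data used: "Data from all patients who had a follow-up visit could be used for the sample size review".
- Success means that the whole 95% interval, by a continuity-corrected Wilson score method, lies below 3.5%. Power is put at 80% with 208 evaluable patients out of 220 randomized.

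On earlier evidence, the Background reports a retrospective comparison of 48 SPD and 65 SDD patients that "found lower mortality rates and fewer serious complications in the group treated with SPD with no difference in recurrence rate of cSDH", and a randomized study with 25 per group in which recurrence was judged equal.

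**The concern.** The 7% is used for two different quantities. It is first the overall recurrence rate with both arms pooled, and then the gap between the arms. A blinded review informs the first. It says nothing about the size or sign of the second, because 7% v 7%, 3.5% v 10.5% and 10.5% v 3.5% all pool to 7%.

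The sign is also unclear. The arms are named SDD then SPD and the rates are written 3.5% then 10.5%. Matched in order, SPD is 7 points worse, so the noninferiority hypothesis would be false under the planning assumption itself. The subtraction as printed equals −7, not 7.

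At stake is the power claim for the primary endpoint. Someone told that a noninferiority trial has 80% power will usually suppose that this applies when the treatments are about equally good. Here it requires SPD to have one third of the SDD recurrence rate, and the text does not say so.

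**Working it through.** **Inputs** (Sample Size section): pooled rate 7%; arm rates 3.5% and 10.5%, with (3.5 + 10.5)/2 = 7 and a gap of 7 points; margin 0.035; two-sided 95% interval; 208/2 = 104 evaluable per arm, 110 randomized per arm. Dropout is consistent: 220 × 0.95 = 209, against 208 needed.

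**Interval.** I take the stated method to be the continuity-corrected Wilson limits combined for a difference (Newcombe hybrid). For one arm with p = x/n, q = 1 − p and z = 1.96:

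- l = [2np + z² − 1 − z√(z² − 2 − 1/n + 4p(nq + 1))] / [2(n + z²)]
- u = [2np + z² + 1 + z√(z² + 2 − 1/n + 4p(nq − 1))] / [2(n + z²)]

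Upper limit for SPD minus SDD: U = (p_SPD − p_SDD) + √[(u_SPD − p_SPD)² + (p_SDD − l_SDD)²].

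**Power** = Σ over all (x, y) of Bin(x; n, π_SPD) × Bin(y; n, π_SDD) × 1[U(x, y) < 0.035]. This is exact enumeration in place of the plan's 9999 resamples.

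**Step 1, the plan's own figure.** SPD 3.5%, SDD 10.5%: 78.5% at 104 per arm and 82.6% at 110. The smallest n reaching 80% is 109 per arm. The stated 80% therefore reproduces with SPD as the better arm.

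**Step 2, the order as printed.** SDD 3.5%, SPD 10.5%: the true difference is +7 points, and 7/3.5 = 2 margins. Power is 0.07%.

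**Step 3, other true differences, pooled rate held at 7%.**

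| SPD v SDD | SPD advantage (points) | Power, 104 per arm | Power, 110 per arm |
|---|---|---|---|
| 3.5% v 10.5% | 7 | 78.5% | 82.6% |
| 4.5% v 9.5% | 5 | 56.7% | 61.7% |
| 5% v 9% | 4 | 45% | about 50% |
| 6% v 8% | 2 | 24% | 27.5% |
| 7% v 7% | 0 | 10.4% | 12.1% |
| 10.5% v 3.5% | −7 | 0.07% | 0.07% |

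**Step 4, what equality looks like in the data.** With 7/104 in each arm, p = 0.0673, l = 0.0298 and u = 0.1385. Then U = 0 + √(0.0712² + 0.0375²) = 0.080, or +8.0 points against a limit of 3.5. With 7 SPD recurrences, SDD needs at least 13 for success: U = 3.2 points at 13 and 4.0 at 12.

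**Step 5, dependence on the interval method.** Other 95% methods at 104 per arm (Newcombe without correction, Wald with and without correction) give 80.1% to 87.4% for SPD 3.5% v SDD 10.5%, and 11.4% to 18.0% for 7% v 7%. The contrast does not come from the continuity correction.

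**Step 6, for scale only.** The normal approximation for 80% power at equal 7% rates is n = (1.96 + 0.8416)² × 2 × 0.07 × 0.93 / 0.035² ≈ 834 per arm. With the stated interval about 890 per arm are needed (79.7% at 880, 80.5% at 900).

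**The case against.** The strongest reply is that the printed order is a labelling slip. The subtraction is already garbled, the sample size works only with SPD at 3.5%, and Figure 2, which is not available here, may label the arms. The 10% v 20% assumption belongs to the abandoned superiority design and is weak evidence of the current direction. This reply largely stands. A reader might infer that the trial was planned with SPD worse, but the documents do not support that, because the calculation contradicts it. What remains is that the prose must be corrected. A labelled figure would change neither the confusion of rate with difference nor the power under equal rates.

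Other stronger readings are tempting and go too far:

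- *80% power requires a 7-point SPD advantage whatever the event rate.* This is true only at a pooled rate of 7%. SPD 2% v SDD 8%, a 6-point gap, gives 82.5% at 104 per arm.
- *The 7% rests on 56 patients alone.* The text also cites new studies. The event count is not stated: 4/56 is an inference from 7%, with an exact 95% interval of 2% to 17%. Length of follow-up at the review is not stated either. A higher 12-month rate is hypothetical; a pooled 10% with the same 7-point gap would give 65% power.
- *The Background establishes equal recurrence.* It does not. The retrospective comparison is small, the 25-per-group study had no recurrences, and other SPD series are described as equal or better on outcome and complications. Equality is compatible with this evidence and is a necessary sensitivity case, but it is not the plan's stated expectation.
- *A failed noninferiority test would be read as evidence against SPD.* The article nowhere equates the two. This is a risk of misreading, not something the plan states.

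**Conclusion.** The sentence is wrong as written. It presents a blinded pooled rate as a between-arm difference, and its order of arms and rates conflicts with the calculation it is meant to support. The 80% power depends on an unstated assumption, for which the article gives no support, that SPD recurrence is 7 points lower than SDD recurrence. At a pooled rate of 7% and 104 to 110 per arm, power is about 78% to 83% under that assumption and about 10% to 12% if the drains are equal.

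These figures rest on the hybrid reading of the stated interval, on equal arm sizes, and on 7% being the true 12-month pooled rate. The low power under equality does not depend on the first: it stays at or below 18.0% at 104 per arm under every 95% interval tried at that rate.

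**What to change.** In the Sample Size section:

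1. Say that 7% is the pooled rate, drawn from the new studies and the blinded review, and that the 7-point difference is a separate planning assumption which the blinded review did not provide.
2. Name the arm with 3.5% and the arm with 10.5%, and correct the subtraction.
3. Restate the power as about 80% under a true 7-point SPD advantage at a 7% pooled rate and about 10% under equal rates, with a short table over true differences such as the one above.
4. Say that an interval crossing 3.5% is inconclusive and does not show that SPD is inferior.

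A superiority test after noninferiority is optional. With the stated interval it has 39% (104 per arm) to 42% (110 per arm) power at the planning values. Its error control would have to account for the yearly interim analyses of recurrence in the Monitoring section, so it cannot be called free of alpha cost without further work.

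The cost is a few sentences and a table, and a power statement that reads less favourably. No extra patients are requested; the figure of about 890 per arm is for information only.
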